### Involving social support network

Our general recommendation through the program will be for patients to involve their family and friends in learning and decision-making about transplant. The brochures also recommend that the patient watch the video with other people in their lives who help them make important health decisions, particularly the stories of living donors, and complete the decision aid with them.

### Variables

Before the intervention, a baseline patient survey will measure the following independent variables: participants’ demographic characteristics, socioeconomic derailers to pursuit of transplant, medical mistrust, health-related quality of life (HRQOL), health literacy, and the amount of previous transplant education they have received. It will also assess the following dependent variables: level of current transplant knowledge, current ability to make an informed decision about transplant, self-efficacy to pursue DDKT and LDKT, and steps taken toward transplant. After the intervention, a post-survey will measure key study dependent variables to assess change, including the level of current transplant knowledge, current ability to make an informed decision about transplant, self-efficacy to pursue DDKT and LDKT, and steps taken toward transplant. For patients randomized to receive the *ET@Home* education, it will also assess their experiences with the educational materials through a program evaluation assessment.

#### Outcome measures and research methodology

In order to verify and demonstrate impact on improving knowledge of the process, risks, advantages, and disadvantages of deceased and living donation among dialysis patients, an RCT will be conducted. In this RCT, 1200 CKD patients in the KPSC system will be randomized to one of two education conditions (patient-guided *ET@Home* vs. standard KPSC transplant education, 600 patients per condition). Changes in key outcomes will be assessed comparing patient data collected at baseline and six months post-baseline. The primary outcome measures include patients’ knowledge of CKD and the risks and benefits of transplant and the capacity to make an informed decision about transplant. Additionally, key secondary measures will be examined, including self-efficacy to pursue DDKT and LDKT and steps taken towards transplant.

Comparisons in the two educational conditions’ effectiveness will also occur for patients earlier in the CKD continuum, patients who speak Spanish, and non-White patients.

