## Study design

The purpose of this study is to assess whether the *ET@Home* program can be integrated successfully across a large racially, ethnically, and geographically diverse patient catchment area and to assess its effectiveness to increase knowledge about the risks and benefits of LDKT and increase informed decision-making. The effectiveness of the *ET@Home* program will be evaluated in a randomized controlled trial (RCT) of 1200 Black, Hispanic, Asian, and White patients with stage 3, 4, or 5 CKD. Patients will be randomized to receive: (1) no additional education other than what is provided within KPSC (standard-of-care); or (2) a video-guided, four-part *ET@Home* program delivered by mail and supported through bimonthly postcards and texting over six months. The study has two aims.

### Aim 1

Before intervention, to assess differences in knowledge and decision-making about the opportunities for and risks and benefits of living kidney donation for 1200 CKD Stage 3–5 patients by race/ethnicity and primary language spoken.

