**Fig. 1 Fig1:**
[figure not shown]
Patient Recruitment Flowchart

After completing the initial survey, enrolled participants will be randomized in a 1:1 ratio, stratified by race/ethnicity, language spoken, and CKD stage, to either the *ET@Home* intervention condition or standard KPSC education. The randomization sequence is produced electronically within the data capture system. Once an enrolled participant is assigned to an intervention arm, the study team will send the participant a notification of their assignment. Since this is an educational intervention, neither the study participants nor the study team are blinded to treatment assignment.

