#### Description of patient-guided *Explore Transplant@Home* program

Patients in the *ET@Home* study condition will receive four modules of video and print transplant education over a 6-month period (Table 1). The modules sequentially help patients think through what is important to them, learn what it might be like if they became a kidney recipient or involved a living donor, the risks and benefits of each, and, at the program’s conclusion, make a decision about the best treatment option for them. The four videos and their corresponding print brochures – “Exploring Transplant”, “Kidney Recipients’ Transplant Experiences,” “Living Donors’ Donation Experiences,” and “Making an Informed Choice” – discuss in detail the medical, psychological, and financial risks of being a deceased or living donor. These modules cover ways to slow down kidney disease and include real life quotes and stories from people who have stayed on dialysis, received DDKT and LDKT, or been a living donor. The “Making an Informed Choice” brochure is a decision aid that guides patients in choosing a path that is right for them and provides helpful websites that patients can use as resources to learn more. At the conclusion of the program, patients individually choose which renal replacement treatments may be right for them and plan a set of small steps they want to take next.

**Table 1 Tab1:** *Explore Transplant@Home* Module Content

Module 1: The Basics of Kidney Disease*	General Contents	Brochure	Postcards	Video
	Welcome & Info Card Video #1 (DVD or link)	“Basics of Kidney Disease” o What are kidneys and what do they do? o What is kidney disease? o What are the treatment options for kidney disease? o Why kidney patients get transplant o Why people donate their kidneys	“What is Chronic Kidney Disease?” “How can I slow down kidney disease?” “What are the treatment options for kidney failure?”	“Exploring possible treatment options” This introductory video explores what kidney disease is and what patients can do to slow down kidney disease through different treatment options.
Module 2: What You Need to Know About Kidney Transplants*	General Contents	Brochure	Postcards	Video

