After each module of print and video education is mailed, postcards will be mailed weekly, recapping important content covered within the videos and brochures. Patients will have the opportunity to participate in a texting component of *ET@Home* that also sends educational content through learning reminders and questions by SMS text message each week (Table 2). Study participants will receive text messages daily that include study participation reminders, motivations to continue in the study, CKD facts, recommendations for learning more, and quiz questions to test knowledge. Participation in the text messaging portion of the trial is voluntary, and the option to opt out is available at all times.

**Table 2 Tab2:** Examples of ET@Home Text Messages

REMINDER	Your first packet “Basics of Kidney Disease” is headed your way! Keep an eye out for the postcards for this packet as well.
MOTIVATION	You can slow down how fast your kidneys fail. Learn more about all of your options!
FACT	Did you know that the kidneys help keep bones healthy?
RECOMMENDATION	Chronic kidney disease (CKD) can present itself through a variety of symptoms. It’s important that you familiarize yourself with these symptoms so you can track changes and talk to your doctor.
QUIZ QUESTION	Can you slow down how fast your kidneys fail? Reply with YES or NO.
ANSWER FOR YES	That’s right! You can slow down how fast your kidneys fail.

If patients have questions for their kidney and transplant providers, they are directed to contact the *ET@Home* Help line, which can connect them with their KPSC providers for more information.

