#### Methodology

Patients will be remunerated $20 with a gift card after completing a baseline survey. Most surveys will be completed online by the study participants directly or over the phone with a trained interviewer. Any mailed surveys will be returned to KPSC and entered into the study’s assessment database. A double-data entry method will be used to ensure accurate data entry. Separate databases will be created for each patient’s registration/contact information and assessment data. Each patient will be given a unique, arbitrary study identification number that can be used to associate their contact and registration information and assessment data. Once the 1200 surveys have been collected and entered, this data will be analyzed to determine baseline differences in transplant knowledge, informed decision-making, self-efficacy, and steps toward transplant between patients varying in race/ethnicity, primary language, and CKD stage before patients are given an intervention.

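### The outcome survey is due six months after baseline, but the six-month programme starts later than baseline, so the survey can come before the last part of delivery

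*Protocol article*

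**What the plan says.** All references are to the protocol article.

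- **Survey date.** Under Outcome measures and research methodology: "Changes in key outcomes will be assessed comparing patient data collected at baseline and six months post-baseline". The Power analysis uses the same time point for the primary comparison.
- **Programme length.** Participants in the ET@Home arm "will receive four modules of video and print transplant education over a 6-month period". The Study design section also gives six months: "delivered by mail and supported through bimonthly postcards and texting over six months".
- **Order of events.** Under Study participants: "After completing the initial survey, enrolled participants will be randomized in a 1:1 ratio", followed by a notice of the assigned arm. The baseline answers are also used to decide whether a patient needs a DVD player or a streaming login. Module 1 is mailed after that.
- **Intended order.** The Variables section puts the post-survey after the intervention. The Process evaluation section has intervention participants rate the programme as a whole at the six-month assessment.
- **Baseline analysis.** The Methodology section says "Once the 1200 surveys have been collected and entered, this data will be analyzed to determine baseline differences", and the sentence ends "before patients are given an intervention".
- **Delivery calendar.** The Study design section calls the postcards bimonthly. The programme description says "postcards will be mailed weekly, recapping important content covered within the videos and brochures". Table 1 lists 14 postcards. The same part of the programme description has texts going out both each week and daily.

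**The concern.** The survey clock starts at baseline and the programme clock starts some time later, yet both run for six months. The survey can therefore arrive while the programme is still in progress, although two other sections assume that it has finished.

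Any loss is at the end of the programme, where Module 4 brings the material together for a treatment decision, and the capacity to make an informed decision is one of the primary outcomes. Patients surveyed before the end contribute a smaller effect, and the intent-to-treat analysis rightly keeps them in their arm. The bias is towards no difference. It cannot be repaired after data collection, and a null result would be harder to interpret.

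The Methodology sentence adds a second question: whether delivery waits for the last baseline survey.

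**Working it through.** **1. The plan's own figures.** The article gives no figure for how much of the programme has been delivered at the survey. Its only design calculation is 90% power with 600 completers (300 per arm) and an effect size of 0.25. The two-sided check is Φ(0.25 × √150 − 1.96) = Φ(1.10) = 0.865; with the other stated effect size, 0.257, it is 0.8825. That shortfall is a separate matter. The 0.865 is used here only as a starting value in step 5.

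**2. When the programme ends.** Let L be the lag in weeks from baseline survey to first mailing. A 26-week programme ends at week 26 + L, and the survey is at week 26. The share of programme time after the survey is L/26. The article does not give L, so the values below are assumed.

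| Assumed L (weeks) | Programme ends (months after baseline) | Share after the survey |
|---|---|---|
| 0 | 6.0 | 0% |
| 1 | 6.2 | 1/26 = 4% |
| 2 | 6.5 | 2/26 = 8% |
| 4 | 6.9 | 4/26 = 15% |

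If the programme fills its six months, it is complete at the survey only when L = 0. Randomisation, notification and mailing all come after baseline, so L is above zero.

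**3. What falls in the gap.** Assume four evenly spaced modules (26/4 = 6.5 weeks apart) and weekly postcards. Module 4 is then mailed at week 19.5 + L, and its five postcards follow at one-week steps.

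- L = 1: Module 4 at week 20.5, last postcard at week 25.5. Everything listed in Table 1 is mailed before the survey.
- L = 2: Module 4 at week 21.5, last postcard at week 26.5. One postcard is late.
- L = 4: Module 4 at week 23.5, postcards at weeks 24.5, 25.5, 26.5, 27.5 and 28.5. Three are late.
- The Module 4 brochure and video themselves come after the survey only if L exceeds 26 − 19.5 = 6.5 weeks.

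Alternatively, suppose the last postcard closes the programme at week 26 + L. Module 4 is then mailed at week 21 + L, which is week 25 for L = 4. It still precedes the survey, but with about a week to use it.

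**4. Postcard calendar.** Table 1 gives 3 + 3 + 3 + 5 = 14 postcards. Sent weekly, they need 14 weeks. Sent twice a month, they need 14/2 = 7 months and outlast the survey. Bimonthly can also mean every two months, which would need 28 months. Whether the survey follows delivery depends partly on which statement holds.

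**5. Illustration of dilution.** If the effect were proportional to the share delivered (an assumption), the planned 1.0-point difference would become 0.96, 0.92 or 0.85 points for L = 1, 2 or 4. Power at 300 per arm and effect size 0.25 would go from 0.865 to 0.837, 0.807 or 0.736. Step 3 suggests that proportionality fits poorly, because the late items are mainly recaps of content already sent.

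**6. The Methodology sentence.** Read literally, all 1200 baseline surveys are collected, entered and analysed first, and delivery follows. L for an early enrolee would then include the remaining recruitment time. The Study participants section instead describes each participant moving from survey to randomisation to notification. The article gives no recruitment duration, so no exposure figure can be derived for the literal reading.

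**The case against.** The best defence is that the intended order is clear: the Variables and Process evaluation sections both put the survey after the programme. The article condenses a fuller protocol, and a mailing calendar and survey window would normally be found there, so their absence is no fault. A fixed clock from baseline, identical in both arms and analysed by intent to treat, is a legitimate choice for an effectiveness trial, and any error is conservative. With prompt mailing and weekly postcards, little of substance is late.

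Most of this stands, and it limits the size of the problem. It does not remove the contradiction: a survey fixed at six months from baseline leaves no room for a six-month programme that starts after baseline, so the stated order cannot be relied on.

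A reader might go further and infer that patients are surveyed with little or no programme delivered, or that the whole loss falls on the decision aid. The document supports neither. The first needs the literal reading of the Methodology sentence, which may only say when the baseline data were taken, as Aim 1 does, and which the randomisation section contradicts. It also needs a recruitment time that is not given. The second fails on step 3 of the check: with lags up to about 6.5 weeks and evenly spaced modules, the Module 4 brochure and video go out before the survey.

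**Conclusion.** The point holds as a timing conflict of limited size. The survey date, the programme length and the order of events, taken together, allow the outcome to be measured before the last part of delivery, contrary to two other sections.

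Under a prompt rolling start, 4% to 15% of programme time falls after the survey for assumed lags of 1 to 4 weeks. This is mostly late Module 4 material, and the dilution towards no difference is modest. These figures rest on the assumed lags, and the split by item also assumes even module spacing and weekly postcards. The loss in points or power cannot be derived from the document.

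A large shortfall would arise only if delivery waits for all 1200 baseline surveys, which the article does not establish. This is a cheap improvement worth making before follow-up begins, not a flaw that invalidates the design.

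**What to change.** - **Clock.** Start follow-up at the first module mailing. For controls use the notification date or, if mailing trails notification, a matched mailing date, so that the interval from baseline to survey is the same in both arms.
- **Survey window.** Open the survey in both arms on that clock, after the last scheduled Module 4 item. Carry the new time point through the Outcome measures, Power analysis, Measures and Process evaluation sections so that they agree with the Variables section.
- **Baseline analysis.** State in the Methodology section that collecting and analysing the 1200 baseline surveys does not delay delivery. If batch release is intended, start the clock at release and align the randomisation section with it.
- **Delivery calendar.** Reconcile the two postcard frequencies with each other and with the 14 postcards in Table 1, and reconcile the two text frequencies.

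The cost is protocol wording and a changed survey trigger. Each patient's follow-up survey comes a few weeks later. No extra patients or procedures are needed.

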### Evaluation and statistical analysis plan

#### Power analysis

Based on the following assumptions, we estimated the sample size for the RCT. Using data from previous RCTs [4, 35], a mean knowledge change score of 1.0 points is estimated necessary to be detected among patients receiving *ET@Home* and standard KPSC education. Patients’ baseline transplant knowledge scores will be correlated with those of other patients from the same clinics [intraclass correlation coefficient (ICC) of 0.31]. The variance in knowledge change has both between- and within-cluster components, yielding a pooled standard deviation estimate of 4.0. Participant retention will be 50% at the 6-month assessment. Outcomes will be assessed using two-tailed statistical tests. Type 1 error rate (alpha level) will be set at 0.05. This study design will ensure power of 0.90. Power calculations for this trial are based on all of these factors, which yields a standardized effect size, accounting for clustering of approximately 0.257.

Power analyses based on changes in transplant knowledge, our primary study outcome, are presented. The study design and analyses were treated as a test of the difference between the mean knowledge score change of CKD patients in the *ET@Home* and standard KPSC education (control) conditions six months post-baseline. It is estimated that with 600 completed surveys (50% attrition), there will be a 90% power to detect a 0.25 effect size between two equal-sized groups (control and treatment groups). By stratifying recruitment and randomization by race/ethnicity (Asian, Black, Hispanic, White), primary language spoken (English vs. Spanish), and stage of CKD, according to the table below, this sample size will also have 90% power to detect 1 point differences in change on the transplant knowledge scale between the *ET@Home* and standard KPSC education conditions for these critical subgroups using interaction terms (e.g., treatment by race interaction, language by race interaction). Patients enrolled and randomized are shown in Table 3.

**Table 3 Tab3:** Patients enrolled and randomized

Race/Ethnicity/Language	Stage of CKD			
	3^a^	4	5/ESRD	Total
*English-speaking Asian*	67	67	66	200
*English-speaking Black*	67	66	67	200
*English-speaking White*	67	67	67	200
*English-speaking Hispanic*	67	67	66	200
*Spanish-speaking Hispanic*	133	133	134	400
Total	400	400	400	1200

^a^
*CKD* 3 patient recruitment prioritized based on likelihood to progress

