Next, the effectiveness of *ET@Home* for CKD Stage 3–5 patients to increase LDKT knowledge and decision-making compared to KPSC education, by race/ethnicity and primary language spoken, will be evaluated. First, it will be determined if baseline differences in patient- and clinic-level variables are present using χ2 and Wilcoxon rank-sum tests, and subsequently adjustments for any out-of-balance characteristics in outcome analyses will be made. Differences in changes in transplant knowledge and Self-Efficacy using change scores, defined as the difference between the baseline and post-survey assessments, will be examined. Differences in these outcomes between the educational conditions will be tested using multilevel random effects models with normal outcome distributions, accounting for clustering with a random intercept for CKD clinic. Differences in informed decision-making will be examined using multilevel random effects logistic models. Finally, for the number of new steps taken, differences between the educational conditions in the count of new steps will be analyzed with a multilevel random effects Poisson model.

After the primary analyses are completed, multilevel random effects models will be constructed to examine the heterogeneity of treatment effect (HTE) using interaction terms for the *ET@Home* educational condition by the key patient subgroups by which randomization was stratified, including race, primary language spoken, and stage of CKD. For example, the *ET@Home* educational condition (*ET@Home* vs. SOC) x primary language (English vs. Spanish) interaction term will be tested, enabling us to determine of the *ET@Home* intervention was more or less effective for primarily Spanish-speaking patients than English-speaking patients.

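### The article gives two primary outcomes in one section and one in another, with a single alpha of 0.05 and no rule for what counts as success

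*Protocol article*

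**What the plan says.** The section *Outcome measures and research methodology* states: "The primary outcome measures include patients’ knowledge of CKD and the risks and benefits of transplant and the capacity to make an informed decision". The next sentence lists self-efficacy and steps toward transplant as secondary, so informed decision-making is placed in the primary tier and not merely mentioned near it.

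The *Power analysis* section speaks of one primary outcome: "Power analyses based on changes in transplant knowledge, our primary study outcome, are presented". Its planning values concern knowledge only: "a mean knowledge change score of 1.0 points is estimated necessary to be detected", with variance components "yielding a pooled standard deviation estimate of 4.0". It also states "Outcomes will be assessed using two-tailed statistical tests", "Type 1 error rate (alpha level) will be set at 0.05" and "This study design will ensure power of 0.90". No event rate, effect size or power is given for informed decision-making.

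The *Statistical analysis* section gives each outcome its own model. Knowledge change goes into a multilevel model with a normal outcome. For the other outcome, "Differences in informed decision-making will be examined using multilevel random effects logistic models". That section gives no significance level, testing order or statement of which result makes the trial positive.

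Hypothesis 1 under Aim 2 predicts benefit on both outcomes, joined by the word and.

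**The concern.** The two sections cannot both govern. A reader of the outcomes section would accept a significant result on informed decision-making as a primary result; a reader of the power section would not. If the outcomes diverge, for example knowledge null and informed decision-making significant, the article gives two defensible answers to whether the trial met its primary objective. The trial is unblinded and both outcomes come from surveys, so the choice should be fixed before the data are seen.

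The stake differs by reading. Under an either-or rule without adjustment, the false-positive rate for the primary claim exceeds 5%. Under a both-required rule, the error rate is safe but the power of the joint claim is unstated. If knowledge alone is primary, the outcomes section is wrong.

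**Working it through.** **Inputs from the article.** Two-sided alpha 0.05; difference 1.0 point; SD 4.0; standardized effect 0.25 (1.0/4.0), with 0.257 also quoted as accounting for clustering; 600 completers out of 1200 at 50% retention, hence 300 per arm; stated power 90%. All are in *Power analysis*; 1:1 allocation is in the randomization text.

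**Step 1: the plan's own power figure, knowledge only.** For two equal groups, power ≈ Φ(d·√(n/2) − 1.96), with n = 300.
- d = 0.25: 0.25 × √150 = 3.062; 3.062 − 1.960 = 1.102; power 86.5%.
- d = 0.257: 0.257 × √150 = 3.148; 3.148 − 1.960 = 1.188; power 88.3%.

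The stated 90% is reproduced only approximately, and better at 0.257. That is a separate matter. What counts here is that every input describes knowledge change, so the figure says nothing about informed decision-making.

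**Step 2: what each reading implies.**

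| Reading | Support in the article | Type I error for the primary claim | Does the stated 90% power apply? |
|---|---|---|---|
| Knowledge alone is primary | *Power analysis* | 5% | Yes, it is the knowledge figure |
| Two primaries, both required | Outcomes section; conjunction in Hypothesis 1 | At most 5% | No, joint power is not given |
| Two primaries, either suffices at 0.05 | Outcomes section; no rule excludes it | Above 5%, see step 3 | Not for informed decision-making |

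**Step 3: the either-or reading.** With both null hypotheses true and each test at two-sided 0.05:
- Independent tests: 1 − (1 − 0.05)² = 1 − 0.9025 = 0.0975.
- Upper bound at any correlation (Bonferroni inequality): 0.05 + 0.05 = 0.10.
- Correlated tests: 1 − P(|Z₁| < 1.96 and |Z₂| < 1.96), with the two test statistics bivariate normal with correlation r. The article gives no correlation, so r is assumed.

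| Assumed r | Chance of at least one false positive |
|---|---|
| 0 | 9.75% |
| 0.3 | 9.5% |
| 0.5 | 9.1% |
| 0.7 | 8.3% |
| 0.8 | 7.8% |
| 0.9 | 7.0% |

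**Step 4: the both-required reading.** A false joint claim needs rejection of at least one true null hypothesis, so its probability is at most 0.05. Joint power cannot exceed the smaller of the two individual powers. It is therefore no higher than the knowledge power, and lower unless informed decision-making succeeds whenever knowledge does. It cannot be put as a number, because the article gives no planning values for informed decision-making.

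**Step 5: the price of splitting alpha instead.** At 0.025 per outcome the critical value is 2.241.
- d = 0.25: Φ(3.062 − 2.241) gives 79.4%.
- d = 0.257: Φ(3.148 − 2.241) gives 81.8%.
- 90% power for knowledge at 0.025 would need 398 or 376 completers per arm. At 50% retention that is 2 × 398/0.5 = 1592 or 2 × 376/0.5 = 1504 randomized, against the planned 1200.

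**Step 6: fixed sequence.** Test knowledge at 0.05, and informed decision-making at 0.05 only after knowledge is significant. If the knowledge null is true, any false claim must begin with a false rejection of it, with probability at most 0.05. If only the informed decision-making null is true, a false claim requires rejecting that one, again at most 0.05. The family-wise error is therefore held at 5%, and knowledge keeps its full alpha and its step 1 power.

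**The case against.** The strongest reply is that much of the danger has to be inferred. A reader might conclude that the plan tests each outcome at 0.05 and so gives the trial two chances of success. The article does not say this. Alpha appears once, among the sample-size assumptions, and no section says that either outcome alone suffices. The conjunction in Hypothesis 1 fits a both-required rule, and the power section fits a single primary outcome; neither inflates type I error. This stands, and the figures in step 3 are conditional for that reason. Independence is also the extreme case: two surveys of the same patients after the same education are likely to be positively correlated, which lowers the figure.

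A second reply is that testing order and alpha allocation commonly sit in an analysis plan or full protocol that is not shown. That also stands, and their absence alone would not be a finding. It does not answer the point made here, which is that two printed statements in the same article disagree on how many primary outcomes there are.

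A reader might also infer that the knowledge outcome itself changes between sections, since it is labelled variously as LDKT knowledge, transplant knowledge, and knowledge of CKD and transplant. The *Measures* section describes one scale covering CKD, LDKT and DDKT, so these are best read as loose labels and do not show that different scores are meant.

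**Conclusion.** The contradiction is real and concerns the trial's main claim: two primary outcomes in the outcomes section, one in the power section, with only knowledge powered. Inflated error is a possible consequence, not a stated feature of the plan. It would be up to about 9.8% with independent tests, about 9.1% at a correlation of 0.5 and 7.0% at 0.9, and only if either outcome sufficed at an unadjusted 0.05. If both are required, type I error is controlled, but the 90% power statement does not describe the joint claim. These results rest on assumed correlations and on the usual normal approximation for the test statistics; the contradiction itself rests on no assumption.

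**What to change.** In both *Outcome measures and research methodology* and *Power analysis*, name change in the transplant knowledge score from baseline to six months as the sole primary outcome. State that informed decision-making is tested second, at two-sided 0.05, and only if the knowledge comparison is significant. Put the same order in *Statistical analysis*.

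This changes wording only. It adds no patients, keeps full alpha for the outcome that was powered, and holds the error over both claims at 5%. The small downside is that informed decision-making can be claimed only after knowledge succeeds; otherwise its estimate and interval are reported descriptively.

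If the sponsor prefers to keep both as primary, which Hypothesis 1 would permit, the article should state that both must be significant and restate the 90% power as applying to knowledge alone.
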